### Statistical considerations

#### Statistical analyses

All primary analyses are based on the intention-to-treat method in which each participant is included in the initial randomization group regardless of adherence. START stratification factors, baseline BMI, and gender are included in all statistical models, so the analysis matches the design, and the estimated variance is not biased. Assumptions are verified for all models, and appropriate transformations used when necessary.

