##### Primary aim

The primary aim is the treatment effect on knee pain and maximal compressive force at 18 months. These and all other repeated measures continuous outcomes will be assessed using a mixed effects model including time (6 and 18 months), treatment group, the time × treatment interaction, and further adjusted for gender, baseline BMI, and baseline values of the outcome (i.e., baseline knee pain for knee pain model, baseline compressive force for compressive force model). The treatment effects at 18 months are tested by applying contrast statements to the mixed model, and maximum-likelihood techniques will be used to estimate parameters under the assumption of an AR(1) covariance structure. Each primary outcome will be analyzed at the Bonferroni-adjusted 0.025 level of significance, and pairwise comparisons between intervention groups at 18 months will use a 0.0083 two-sided level of significance (2 outcomes, 3 interventions) [88]. Preliminary analyses are conducted to check the shape of the distributions and variances between groups and as a function of the covariates to ensure residuals are approximately normally distributed. Regression diagnostics and residual plots help find appropriate transformations if necessary. In subsequent models, we will control for possible confounders, including PF OA severity (none to moderate) and use of medications, such as analgesics, NSAIDs, bisphosphonates, and glucosamine/chondroitin sulfate. Because we exclude subjects with severe PF OA and medication has only modest efficacy in OA, we do not expect significant confounding by these variables.

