#### Sample-size calculations

##### Primary outcomes

A total sample of 372 (124/group) provide 80% statistical power to detect differences ≥17.6% in pain and ≥9.6% in maximal compressive force at the 2-sided 0.0083 significance level with 80% retention (2-sample *t*-test, Nquery Advisor). Standard deviations for pain and maximal compressive force were obtained from the START pilot (unpublished) and ADAPT [58,59] which measured the same outcomes and used similar patient populations; with mean differences of 1.12 (18%) and 657 N (20%), respectively.

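### With only two visits, the AR(1) covariance forces one variance at 6 and 18 months, so the 18-month standard error is right only if residual spread is equal; an unstructured covariance removes the constraint at almost no cost

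*Protocol article*

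**What the plan says.** All of this comes from the protocol article, under Statistical considerations.

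- **Model (Primary aim).** Knee pain and maximal compressive force are each analysed with a "mixed effects model including time (6 and 18 months), treatment group", the interaction of the two, gender, baseline BMI and the baseline value of the outcome. Baseline is thus a covariate, and the repeated response has two occasions.
- **Covariance (Primary aim).** "maximum-likelihood techniques will be used to estimate parameters under the assumption of an AR(1) covariance structure".
- **Test (Primary aim).** "The treatment effects at 18 months are tested by applying contrast statements to the mixed model".
- **Levels (Primary aim).** The overall error rate is split by Bonferroni, which leaves 0.025 for each of the two outcomes. For the pairs of arms, the rule reads: "pairwise comparisons between intervention groups at 18 months will use a 0.0083 two-sided level of significance (2 outcomes, 3 interventions").
- **Checks.** The Statistical analyses section says: "Assumptions are verified for all models, and appropriate transformations used when necessary". The Primary aim section adds preliminary checks of distribution shape and of "variances between groups and as a function of the covariates", with residual plots used to look for a suitable transformation.

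No heterogeneous or unstructured covariance, and no robust standard error, is named as an alternative.

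**The concern.** Standard AR(1) has two parameters, a variance and a correlation. Over three or more visits it describes a correlation that decays with the gap between visits. Over two visits there is only one gap and so no decay to describe. What remains is one correlation, estimated freely, and one variance shared by both visits, which is compound symmetry.

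The shared variance is the difficulty. Both primary outcomes are judged at 18 months, yet the standard error of that contrast averages the residual spread at 18 months with that at 6 months. If the two differ, the standard error, confidence interval and p-value at 18 months are off, and the pairwise tests do not run at the level the article sets.

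The spread that matters is the residual spread after adjustment for baseline, BMI and gender. Equal raw SDs at the two visits would not settle the question, because the association with baseline may weaken between 6 and 18 months.

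**Working it through.** **1. The plan's own level.** There are two outcomes and three pairs, so 0.05 / 6 = 0.025 / 3 = 0.00833. This reproduces the stated 0.0083. The two-sided critical value for 0.0083 is z = 2.640.

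**2. Inputs.** From the article: two post-baseline visits, AR(1), maximum likelihood, a test at 18 months, 124 randomised per group and 80% retention (about 99 per group at 18 months). Assumed, because the article gives no SD by visit: r, the residual SD at 18 months divided by the residual SD at 6 months, taken from 0.8 to 1.5.

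**3. Closed form, complete data.** Set the 6-month residual variance to 1, so that the 18-month variance is r². The model uses their average, (1 + r²)/2, at both visits. Hence:

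- k = model SE / true SE at 18 months = √[(1 + r²) / (2r²)]
- true level = 2 × [1 − Φ(2.640 × k)]

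Worked case, r = 1.2: (1 + 1.44) / 2.88 = 0.847; k = 0.920; 2.640 × 0.920 = 2.430; level = 0.0151.

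| r | k | True level of the 0.0083 test | 6 × level |
|---|---|---|---|
| 0.8 | 1.132 | 0.0028 | 0.017 |
| 0.9 | 1.057 | 0.0053 | 0.032 |
| 1.0 | 1.000 | 0.0083 | 0.050 |
| 1.1 | 0.956 | 0.0117 | 0.070 |
| 1.2 | 0.920 | 0.0151 | 0.091 |
| 1.3 | 0.892 | 0.0185 | 0.111 |
| 1.4 | 0.869 | 0.0218 | 0.131 |
| 1.5 | 0.850 | 0.0249 | 0.149 |

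The last column is the Bonferroni bound over all six primary comparisons if r is the same for both outcomes.

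**4. Simulation with dropout.** Maximum-likelihood fits, 8,000 trials per scenario, 3 × 124 randomised, 99 per group seen at 18 months. Further assumptions: 112 per group seen at 6 months, correlation 0.6 between visits, baseline coefficient 0.5. "Empirical SE" is the SD of the AR(1) estimates over the simulated trials.

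| r | AR(1) mean SE | Empirical SE | AR(1) level | Unstructured mean SE | Unstructured level |
|---|---|---|---|---|---|
| 0.8 | 0.126 | 0.111 | 0.0030 | 0.111 | 0.0091 |
| 1.0 | 0.138 | 0.138 | 0.0084 | 0.138 | 0.0086 |
| 1.1 | 0.145 | 0.154 | 0.0138 | 0.152 | 0.0093 |
| 1.2 | 0.152 | 0.167 | 0.0164 | 0.166 | 0.0085 |
| 1.3 | 0.159 | 0.182 | 0.0234 | 0.180 | 0.0108 |
| 1.5 | 0.175 | 0.210 | 0.0285 | 0.208 | 0.0084 |

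The Monte Carlo standard error of a level near 0.0083 is √(0.0083 × 0.9917 / 8,000) ≈ 0.001. The simulation follows the closed form and runs somewhat above it when r exceeds 1, in part because dropout gives the 6-month data more weight in the pooled variance. A separate, smaller simulation at r = 1.4 (correlation 0.5, 20% missing at 18 months) gave 0.024 under AR(1).

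**5. Equal raw SDs are not enough.** Suppose raw SDs are equal, but correlation with baseline falls from an assumed 0.6 at 6 months to 0.45 at 18 months. Then r = √[(1 − 0.45²) / (1 − 0.6²)] = √(0.7975 / 0.64) = 1.116, and the true level is 0.0122.

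**The case against.** The strongest reply is that the harm is assumed. The article prints no SD at 6 or at 18 months; the sample-size section names the sources of its SDs but gives neither values nor visits. Spread might be stable. It might also fall, since WOMAC pain is bounded at 0–20, and the test would then be conservative. Ratios of 1.2 and 1.4 mean residual variances 44% and 96% higher at 18 months, which is not a small change. All of this stands, and it is why the result is given as a range on both sides of 1.

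A reader might infer that responses must diverge over 18 months, given the expected 65% adherence, and that the primary tests are therefore too liberal. The article does not support this. The 65% is an estimate of attendance and says nothing about the spread of outcomes.

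A reader might also object that AR(1) would impose an implausible decay through a 12-month visit. The primary model has no 12-month visit, so the argument does not apply.

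The second reply is that the article promises to verify assumptions for every model, and that fallback detail commonly sits in an analysis plan. This stands in part: the general check might reveal unequal variances. But the variance checks listed are across groups and covariates, and a transformation does not release the covariance constraint. The covariance structure is also stated outright in the article, so this is not a question of missing detail.

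Third, the alternative is not perfect: its simulated level reaches 0.0108 in one scenario. That is slightly above nominal, but far closer than AR(1) in the same scenario (0.0234).

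**Conclusion.** The point holds in conditional form. The stated model fixes equal residual variances at 6 and 18 months, and nothing else in the article relaxes this. If the variances are equal, the 18-month test is exact and nothing is lost. If they differ, the true level of the nominal 0.0083 test is about 0.003 at a residual SD ratio of 0.8, 0.012 at 1.1, 0.015 at 1.2, 0.022–0.025 at 1.4 and 0.025–0.029 at 1.5. Below 1 the cost is power; above 1 it is type I error. The article gives no basis for placing either outcome within that range.

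The fault lies in the standard error, confidence interval and p-value. The 18-month point estimate is hardly affected. The sample size rests on a two-sample t-test and does not depend on this choice.

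The conclusion reads AR(1) as the usual homogeneous form. Adding a random intercept would still give equal variances. A heterogeneous AR(1) or a random slope would not, but the article states neither. The mechanism is certain and its occurrence is unknown, so this is a free improvement.

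**What to change.** In the Primary aim section, replace the AR(1) assumption with an unstructured covariance for the 6- and 18-month residuals, so that each visit has its own variance.

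With two visits this means three covariance parameters in place of two, with about 99 participants per group (some 297 in all) expected at 18 months. If the variances are equal, the standard error is the same under both structures (0.138 in the simulation), so the constraint buys no precision that would be given up. The change is one line of wording.

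REML with Kenward-Roger degrees of freedom would be a reasonable refinement but is optional: no harm from maximum likelihood was shown at this sample size.

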##### Secondary outcomes

Overall, our sample size provides a moderate effect size of 0.46 with relevant detectable differences. ADAPT’s largest effect on WOMAC function was a 17% relative decrease. We are able to detect differences in thigh-muscle volume smaller than 10%. Goopaster [92] showed that after 12 months mean thigh-muscle attenuation significantly decreased by 1.4 HU in a control group but not in a physical activity group. With 6 more months of physical activity, we expect to detect group differences as small as 2.3 HU. A magnitude of 22% reduction in IL-6 is similar to reductions seen in clinical trials of statins and other anti-inflammatory medications [93-98].

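### The six primary pairwise contrasts use single-step Bonferroni, which is valid but dominated by Holm at the same 5% familywise error; the gain for pain (high intensity versus control) is near zero to about 5 points

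*Protocol article*

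**What the plan says.** The Primary aim paragraph of the protocol article sets two levels. For the outcomes: "Each primary outcome will be analyzed at the Bonferroni-adjusted 0.025 level of significance". For the contrasts: "pairwise comparisons between intervention groups at 18 months will use a 0.0083 two-sided level of significance (2 outcomes, 3 interventions". No ordering, weighting or passing-on of alpha is described.

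The sample-size section (Primary outcomes) plans at the same two-sided pairwise level of 0.0083 and assumes that four in five participants are retained. Its claim is: "A total sample of 372 (124/group) provide 80% statistical power to detect differences ≥17.6% in pain and ≥9.6% in maximal compressive force". On the source of the spread it says "Standard deviations for pain and maximal compressive force were obtained from the START pilot (unpublished) and ADAPT", and the sentence ends "with mean differences of 1.12 (18%) and 657 N (20%), respectively". The standard deviations themselves are not printed.

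The abstract names pain as the primary clinical aim and knee compressive force as the primary mechanistic aim.

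**The concern.** Splitting 0.05 into two fixed halves, and each half into three, gives every contrast 0.05/6 whatever the other five show. The protocol's own percentages suggest that the two outcomes are unequally placed. The pain difference of 18% is 1.02 times its detectable limit of 17.6%. The force difference of 20% is 2.08 times its limit of 9.6%. If force contrasts are clearly significant, the error allowance spent on them is no longer needed, yet pain is still judged at 0.0083. At stake is some power on the primary clinical outcome that could be had without more participants and without relaxing the 5% familywise error.

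**Working it through.** **Inputs.** From the protocol: 124 per arm, 80% retention, two-sided 0.0083, 80% power, detectable differences 17.6% (pain) and 9.6% (force), mean differences 1.12 (18%) and 657 N (20%). Assumed, because the protocol does not give them: the low-intensity effect and the correlation between outcomes.

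**1. The plan's own figures.**
- Levels: 0.05/2 = 0.025 and 0.025/3 = 0.05/6 = 0.0083. Both match.
- Sample size: the secondary-outcome section states that "our sample size provides a moderate effect size of 0.46 with relevant detectable differences". With d = 0.46, the secondary pairwise level of 0.0167 and 80% power, the normal formula n = 2(z₁₋α/₂ + z₀.₈)²/d² gives 99 completers per arm. Then 99/0.80 = 123.75, so 124. This matches.
- Primary outcomes: at 99 per arm and 0.0083, the effect detectable with 80% power by a two-sample t-test is d = 0.499. The SDs are not printed, so the 80% claim cannot be rebuilt independently and serves as the anchor. Back-solved SDs are 0.176 × (1.12/0.18)/0.499 ≈ 2.2 points for pain and 0.096 × (657/0.20)/0.499 ≈ 632 N for force.

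**2. Power at the printed differences (unadjusted t-test, 99 per arm).**
- Pain: d = 0.499 × 18/17.6 = 0.511. Power is 82.1% at 0.0083. If 18% is a rounded figure (17.5 to 18.5), power is 79% to 85%.
- Force: d = 0.499 × 20/9.6 = 1.040. Power is above 99.99%.
- If all three force contrasts are rejected, Holm tests the smallest pain p-value at 0.05/3 = 0.0167. Pain power at that level is 87.9%.
- To reach that power at 0.0083 by enrolment would take about 114 completers per arm: 114/0.80 = 142.5, so 143, and 3 × (143 − 124) = 57 more participants.

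**3. Dominance.** Holm orders the six p-values and compares them with 0.05/6, 0.05/5, ..., 0.05/1, stopping at the first failure. Any p-value at or below 0.05/6 is always rejected, so Holm never rejects fewer contrasts than the present rule. It controls the familywise error at 0.05 under any dependence. This step needs no assumption about effect sizes.

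**4. Size of the gain for pain, high intensity versus control.** Simulation with 99 per arm, normal approximation, low-intensity effect at half of high on both outcomes, between-outcome correlation 0.2. The starting value is 83% rather than 82.1% because the simulation uses the normal approximation.

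| Force effect, high intensity versus control | Present rule | Holm over six |
|---|---|---|
| 20% | 83% | 88% |
| 9.6% | 83% | 85% |
| half of 9.6% | 83% | 83.5% |
| none | 83% | 83% |

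The simulated familywise error of Holm did not exceed 0.046 in the null configurations tried. With no pain effect and force effects in all three pairs, the present rule spends only about 0.023 of its 0.05.

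**5. Baseline adjustment.** The planned model adjusts for baseline. If the back-solved SD is unadjusted and the baseline correlation is r, d becomes d/√(1 − r²). Pain power at 0.0083 versus 0.0167 is then 86% versus 91% for r = 0.3, and 93% versus 96% for r = 0.5. The protocol does not say which kind of SD was used.

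**The case against.** The present rule is valid, prespecified and consistent with the sample-size section, and on the printed figures pain has more than 80% power. All of that stands. A reader might infer that the split is an error or leaves pain underpowered. The document supports neither.

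A reader might also infer that the plan itself claims near-certain power for force. It does not. The 18% and 20% stand in the sentence on where the SDs came from, and they are not labelled as the effects expected in this trial. The Discussion treats the effect of strength training on joint loading as still to be determined. The pain gain therefore depends on a force result that is open, as the table shows.

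A larger gain is tempting for high versus low intensity on pain: 20% to 34% in the first scenario of the table. It rests on a low-intensity effect that the protocol does not give, and it mixes steps within pain with steps between outcomes. A closed test within pain alone at 0.025, with the split untouched, already gives about 32%. Holm over six contrasts is also not the same procedure as a closed test within each outcome with alpha passed between outcomes. The latter gives 89% and 41% in that scenario, against 88% and 34% for Holm.

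Two costs are real. Bonferroni has directly matching simultaneous intervals (99.17% per contrast), and Holm has no simple equivalent. Under Holm the pain threshold also depends on a model-estimated gait force, so the clinical and mechanistic aims are no longer judged separately. These costs are small, but they are a fair reason for a team to weigh the choice.

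**Conclusion.** The point holds as a cheap gain in efficiency, not as a fault in error control. Single-step Bonferroni over the six primary contrasts can be replaced by Holm, which never rejects less at the same 5% familywise error; that part is free of assumptions. The size is not. Under the half-effect assumption for low intensity, and before baseline adjustment, pain for high intensity versus control gains about 5 points if force reaches 20%, about 2 if it is at 9.6%, and almost nothing if force has no effect. Baseline adjustment may shrink these gains; at the 0.0167 level the difference is about 3 points if the baseline correlation is 0.5. No single figure can be given for high versus low intensity, because the protocol states no low-intensity effect.

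**What to change.** In the Primary aim paragraph, before any outcome data are seen, replace the 0.025 per-outcome level and the fixed 0.0083 with one rule: the six 18-month pairwise p-values (two outcomes, three pairs) are ordered and tested by Holm at 0.05/6, 0.05/5, ..., 0.05/1. Say that any overall test per outcome is then descriptive. Leave the sample-size section at 0.0083 as the conservative planning level.

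The cost is one sentence in the plan, with no extra participants or data. The report needs a line saying that each threshold depends on the other contrasts. It should also say which intervals are shown: unadjusted or Bonferroni intervals can stand alongside the Holm decisions, with a note that they need not agree with them in every case.

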## Methods/Design

### Study design

START is an assessor-blinded, single-center, 18-month, parallel design randomized controlled trial. Participants are randomized into one of 3 groups: high-intensity strength training (H), low-intensity strength training (L), or healthy living education (C).

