##### Secondary aims

Standard repeated measures mixed models (including adjustment variables as noted above) are used for secondary aims at the 0.05 significance level, with pairwise treatment group comparisons performed at the 0.0167 significance level for testing 18 month effects. Short-term effects are determined by using contrast statements comparing 6-month treatment effect means from primary and secondary outcome models. Outcomes assessed at baseline and 18 months only (MoCa, DXA measures, and Knee PA x-ray) will be compared using an ANCOVA model for treatment effects adjusting for baseline BMI, gender, and baseline values of the outcome.

As inflammatory marker distributions are often skewed, data are log-transformed before analysis. The effect of the interventions at 18 months is determined with repeated measures mixed models and estimates obtained at each visit. For ease of interpretation, transformed log means and standard errors back to their original units are used.

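### With three arms, a fixed 0.0083 for every pairwise test is valid but more conservative than the 0.025 per primary outcome requires; a written step-down rule would recover power at no sample-size cost

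*Protocol article*

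**What the plan says.** The Study design section describes three arms: "Participants are randomized into one of 3 groups: high-intensity strength training (H), low-intensity strength training (L), or healthy living education (C". Under Primary aim there are two co-primary outcomes: "The primary aim is the treatment effect on knee pain and maximal compressive force at 18 months". The article sets two levels for them. First, "Each primary outcome will be analyzed at the Bonferroni-adjusted 0.025 level of significance". Second, "pairwise comparisons between intervention groups at 18 months will use a 0.0083 two-sided level of significance (2 outcomes, 3 interventions". The tests come from one model: "The treatment effects at 18 months are tested by applying contrast statements to the mixed model".

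Secondary aims follow the same pattern. Mixed models "are used for secondary aims at the 0.05 significance level, with pairwise treatment group comparisons performed at the 0.0167 significance level".

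The sample-size section uses the pairwise level: "A total sample of 372 (124/group) provide 80% statistical power to detect differences ≥17.6% in pain and ≥9.6% in maximal compressive force", at two-sided 0.0083 with 80% retention.

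The article does not say what test is performed at 0.025. Nor does it say whether the pairwise tests depend on its result.

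**The concern.** A fixed Bonferroni division by three treats the three pairwise nulls as if any combination of them could be true. With three means that is not so: if two of the equalities hold, the third follows. The number of true nulls can only be three, one or none, never two. Dividing by three is therefore needed only while all three nulls may be true. Once one pair has been shown to differ, at most one null remains true, and each remaining pair can be tested at the full 0.025.

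Power is what is at stake. The fixed rule leaves part of the allotted error unused in the configurations where one comparison has already succeeded. The loss falls mostly on the second and third comparisons. If the low-intensity arm lies between the other two, those include high versus low intensity.

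**Working it through.** **Inputs.** Three arms (Study design); two primary outcomes, 0.025 per outcome and 0.0083 per pair (Primary aim); 0.05 and 0.0167 (Secondary aims); 124 per arm, 80% retention, 80% power, detectable differences of 17.6% in pain and 9.6% in force (Sample-size calculations). The standard deviations are not printed, so differences are expressed as d, in SD units.

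**1. The plan's own figures.**
- Level: 0.05/(2 × 3) = 0.025/3 = 0.00833, as stated. Secondary: 0.05/3 = 0.0167, as stated.
- Completers: 124 × 0.80 = 99.2, taken as 99 per arm.
- Detectable difference: d = (z for the two-sided level + z for 80% power)/√(n/2), with √(99/2) = 7.036.
  - At 0.0083: (2.640 + 0.842)/7.036 = 0.495; with the t distribution, 0.499.
  - At 0.0167: (2.393 + 0.842)/7.036 = 0.460, which matches the 0.46 given for secondary outcomes.

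The plan is therefore consistent with itself.

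**2. Error control by closure, for one outcome.**
- All three means equal: Shaffer's rule makes a first rejection only if the smallest p is below 0.0083, so the error is at most 3 × 0.0083 = 0.025. The gated rule makes one only if the 2-df test is significant at 0.025.
- Exactly one pair equal: only one false positive is possible, and it is tested at 0.025 at most.
- No pair equal: no false positive is possible.

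Both rules thus control the familywise error strongly at 0.025 per outcome, hence at most 0.05 over the two outcomes. The division by two for the two outcomes is still needed.

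**3. Simulated familywise error per outcome** (1,000,000 trials, 99 per arm, normal data, equal variance, pooled SD).

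| Rule | All arms equal | One pair equal, third arm 0.499 SD away |
|---|---|---|
| Pairs at 0.0083, no gate | 0.023 | 0.008 |
| Shaffer | 0.023 | 0.025 |
| Gate 0.025, then pairs 0.025 | 0.025 | 0.025 |
| Pairs at 0.025, no gate | 0.064 | 0.025 |

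**4. Pairwise power at d = 0.499**, the difference with 80% power at 0.0083.

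| Pattern and contrast | Pairs at 0.0083 | Shaffer | Gated |
|---|---|---|---|
| One arm apart, either true contrast | 0.80 | 0.86 | 0.88 |
| L midway, H vs C | 0.80 | 0.81 | 0.82 |
| L midway, H vs L or L vs C | 0.19 | 0.30 | 0.31 |
| Arms at 0, d, 2d, adjacent contrasts | 0.80 | 0.895 | 0.895 |

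**5. Detectable difference with the gate.** A single test at 0.025 has 80% power at d = 0.441, but the gate must also be passed. At d = 0.441 the gated rule has only about 77% power (one arm apart) or 70% (H vs C, L midway). For 80% it needs d of about 0.457 or 0.488. Scaling the stated percentages in proportion to d:
- Pain: 17.6% × 0.457/0.499 = 16.1%, or 17.6% × 0.488/0.499 = 17.2%.
- Force: 9.6% × 0.457/0.499 = 8.8%, or 9.6% × 0.488/0.499 = 9.4%.

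**The case against.** The strongest reply is that nothing here is wrong. The single Bonferroni rule is valid, the trial is sized at the same 0.0083, and the stated 80% power already includes the correction. The rule lets any pair be declared without a prior test, and it comes with simultaneous intervals that agree with the tests. All of this stands, and it is why the point is an efficiency suggestion.

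Three stronger readings are tempting, and the article does not support them.

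- A reader might infer that the plan corrects twice, first with an overall test at 0.025 and then with a division by three. The separate 0.025 level invites that reading. But no overall test or gate is written, and 0.025 may simply be each outcome's share of 0.05. In that case 0.0083 is one ordinary Bonferroni step. The efficiency point survives on either reading, because Shaffer's rule keeps every rejection that the ungated 0.0083 rule makes and adds others.
- A reader might infer that the division by three protects nothing. As the plan is written it does protect: without it and without a gate, the error is about 0.064 per outcome.
- A reader might infer that the detectable difference in pain falls to about 15.5% (17.6% × 0.441/0.499). That ignores the gate; step 5 gives the correct range.

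It is also fair to say that high versus low intensity stays badly underpowered if the low arm is midway, at 0.30 to 0.31. The article does not rank the three contrasts and states no expected difference between the two training arms.

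**Conclusion.** The point holds as a cheap improvement to a valid, conservative plan. At the same familywise limit of 0.025 per primary outcome, a comparison planned at 80% power would have between about 81% and 90%, depending on where the third arm lies. The gain is 6 to 8 points with one arm apart. It is only 1 to 2 points for high intensity versus control when low intensity is midway, and there the half-size contrasts gain about 11 to 12 points. With a gate, the difference in pain detectable with 80% power is about 16.1% to 17.2% in these two patterns, instead of 17.6%.

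The error argument rests on there being exactly three arms and carries over to the 18-month contrasts of the mixed model. The power figures assume 99 completers per arm, equal variances and a plain three-group comparison. They also depend on the arm patterns chosen, which are illustrative and not taken from the article.

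**What to change.** Under Primary aim, replace the fixed pairwise level with one of two written rules for each primary outcome:

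- Shaffer's step-down (the simpler choice): test the smallest of the three pairwise p-values at 0.0083; if it is significant, test each of the other two at 0.025.
- Gated version: test the 2-df arm effect at 18 months at 0.025; only if it is significant, test each pair at 0.025.

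Under Secondary aims use 0.0167 then 0.05, or a 0.05 gate then 0.05. The step or gate has to be stated explicitly.

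The cost is a sentence in each of the two sections. The sample-size section can keep 0.0083 as a conservative basis. There are two downsides. Unadjusted 97.5% pairwise intervals are not simultaneous and may not agree with the test decisions, so the report should say so. Under the gated version a pair with p below 0.0083 can fail the gate; this happened in under 1% of simulated trials, and Shaffer's rule avoids it.
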